### Sample Size and Retention

The sample of 210 enables detection of a small effect size of *f*
^
*2*
^=.046 in the multiple regressions. Although the study uses all allocated participants in the outcome analyses, efforts are made to maximize retention by maximizing rapport at the baseline assessment and collecting multiple means to contact participants, including email, landline, and mobile phone contact details, and by assertive follow-up. With these strategies, the study is aimed to have at least 70% retention at 12 months.

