**Methods:**

A small pilot trial is conducted that primarily tests program functionality, efficacy, and user acceptability and satisfaction. This is followed by the main RCT, which compares 3 treatments: (1) delayed program access: usual diabetes care for 3 months postbaseline followed by access to the full OnTrack Diabetes program; (2) immediate program: full access to the self-guided program from baseline onward; and (3) immediate program plus therapist support via Functional Imagery Training (FIT). Measures are administered at baseline and at 3, 6, and 12 months postbaseline. Primary outcomes are diabetes self-care behaviors (physical activity participation, diet, medication adherence, and blood glucose monitoring), glycated hemoglobin A1c (HbA1c) level, and diabetes-specific distress. Secondary outcomes are depression, anxiety, self-efficacy and adherence, and quality of life. Exposure data in terms of program uptake, use, time on each page, and program completion, as well as implementation feasibility will be conducted.

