### Recruitment and Sample

Recruitment strategies for the trial are primarily community-based: newspaper advertisements, health organization newsletters, radio broadcasts, notice board postings, bulletins, emails, and online advertisements. Targeted methods include the distribution of study flyers and posters to medical centers, letters to health institutions, pharmacies and health professionals, and featuring the OnTrack Diabetes website URL on statewide Diabetes Australia research Web pages. Attendance at diabetes-related expos and events allows in-person recruitment and further promotion of the project to health professionals.

The trial aims to enroll at least 210 participants. Selection criteria include (1) type 2 diabetes diagnosis (by a medical doctor and according to World Health Organization criteria) of at least 3 months duration, (2) age 18 years or older, (3) living in Australia without plans to leave within 12 months, (4) regular computer and Internet access, (5) contactable by phone, (6) clear command of written English (at least Year 5 education), and (7) stable diabetes pharmacotherapy (medication dose stable ≥4 weeks; medication type stable ≥3 months). Study exclusion criteria include (1) current diagnosis of mental disorder other than depression or anxiety (participant is asked if a condition has been diagnosed and if so they are informed that they will receive access to the program but not be included in the trial), (2) current suicidal risk (assessed via suicide risk assessment), (3) significant cognitive disorder (eg, from head trauma or dementia), (4) currently on steroid medication or likely to commence it in the next 12 months, and (5) pregnant or likely to become pregnant in the next 12 months.

All participants are asked to undertake a medical assessment by their general practitioner prior to study enrollment. Individuals with physical limitations or concurrent physical disorders are advised of the need to exercise caution in setting physical activity goals according with their doctor’s advice.

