### Statistical Analyses

Preliminary analyses assess for baseline differences and subsequent analyses control for any observed differences. The primary analyses will comprise multiple regressions, predicting posttreatment and follow-up results from baseline measures and treatment contrasts with multiple imputation being used to predict missing data. Mixed-model ANOVAs with repeated measures will also be applied to confirm whether effects are still obtained without imputations. Both methods allow an intention-to-treat approach to the data. Repeated measures ANOVAs will be used to evaluate differences in change scores between the study time points among the 3 study conditions.

User satisfaction, perceived ease of use, and usefulness are examined with ANOVAs and program reach, acceptability, implementation feasibility, and outreach are assessed using the Reach Effectiveness Adoption Implementation Maintenance (RE-AIM) framework [64]. This will be operationalized using the OnTrack Diabetes Evaluation Questionnaire, which asks about users’ perceptions of the program’s acceptability, issues with feasibility, and outreach (ie, ability to access the program and barriers to access including poor broadband network availability). The inclusion of residents of rural and regional areas enriches this evaluation as will quantitative data about participants’ exposure to the program.

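### The detectable effect of f² = .046 is tied to all 210 enrolled participants, with no stated allowance for the attrition accepted at 12 months

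*Protocol article*

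**What the plan says.** In the protocol article, Recruitment and Sample sets the target: "The trial aims to enroll at least 210 participants". Sample Size and Retention uses the same number for its sensitivity claim: "The sample of 210 enables detection of a small effect size" of f² = .046, for the multiple regressions. It goes on: "Although the study uses all allocated participants in the outcome analyses", efforts are made to keep people in, and "the study is aimed to have at least 70% retention at 12 months".

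Statistical Analyses makes multiple regressions primary. They predict post-treatment and follow-up results from baseline measures and "treatment contrasts with multiple imputation being used to predict missing data". The abstract describes a main trial "which compares 3 treatments". Under Design and Setting, the hypothesis that immediate access plus Functional Imagery Training does best is placed at 3 months.

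The article gives no alpha, power or number of tested degrees of freedom for .046, and no retention figure for 3 or 6 months.

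**The concern.** The number enrolled and the number behind the detectable effect are the same 210. The figure therefore contains no visible margin for loss, although the paragraph accepts up to 30% loss by 12 months. The clause about analysing everyone allocated could suggest that 210 survives dropout because missing values are imputed. Imputation keeps 210 rows in the regression, but it does not supply the information in outcomes that were never observed.

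What is at stake is how follow-up results are read. The primary regressions cover follow-up as well as post-treatment, and the Discussion relies on the 12-month data for maintenance of effects. If the published sensitivity is better than the trial will have at that visit, a null result there will be taken as stronger evidence against an effect of f² = .046 than it is.

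**Working it through.** **Inputs from the article.** N = 210 (Recruitment and Sample; Sample Size and Retention). Detectable f² = .046. Retention of at least 70% at 12 months, so 210 × 0.70 = 147. Three arms, so an overall arm test has 2 df.

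**Assumed, because not stated.** Power 80%, and three readings of alpha and tested df:
- A: 2-df arm test, alpha .05
- B: 1-df contrast, alpha .025
- C: 1-df contrast, alpha .05

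**Formula.** Noncentral F test in multiple regression, with noncentrality λ = f² × N and denominator df = N − p − 1. I take p = 3 predictors (baseline plus two arm terms); changing p up to 10 moves the f² results by no more than about .0001. Power = P[F′(df1, N − p − 1; λ) > the central F critical value]. The detectable f² is the value at which power is .80.

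**Step 1: reproduce the stated figure at N = 210.** For f² = .046, λ = .046 × 210 = 9.66.

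| Reading | Detectable f² at 210 | Power for .046 at 210 | N needed for .046 |
|---|---|---|---|
| A | .0466 | 79.5% | 213 |
| B | .0458 | 80.2% | 210 |
| C | .0377 | 87.2% | 173 |

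A and B reproduce .046 with all 210 complete. C does not; it would give .038 at 210. A search over alpha .025, .05 and .10, power 70%, 80% and 90%, and 1 to 5 tested df found no combination that needs about 147 for .046. So the figure does not appear to have been derived at the retained number.

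**Step 2: 12 months, 147 complete cases.** For f² = .046, λ = .046 × 147 = 6.76.

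| Reading | Detectable f² at 147 | Power for .046 at 147 |
|---|---|---|
| A | .0669 | 63.0% |
| B | .0658 | 63.2% |
| C | .0541 | 73.3% |

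Simple scaling agrees with A and B: .046 × 210/147 = .0657.

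**Step 3: what imputation might recover at 12 months.** Let r² be the assumed share of the missing values explained by baseline and earlier visits. As an approximation, effective N = 147/(1 − 0.3 × r²), which gives 147 at r² = 0 and 210 at r² = 1.
- r² = .25: 147/0.925 = 159. Detectable f² is .062 (A), .061 (B), .050 (C); power for .046 is 67%, 67%, 77%.
- r² = .50: 147/0.85 = 173. Detectable f² is .057 (A), .056 (B), .046 (C); power is 71%, 71%, 80%.

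**Step 4: 3 months, with retention assumed at 80–90%.** 210 × 0.80 = 168; 210 × 0.90 = 189.

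| Reading | f² at 168 | Power for .046 | f² at 189 | Power for .046 |
|---|---|---|---|---|
| A | .0584 | 69.3% | .0518 | 74.8% |
| B | .0575 | 69.7% | .0510 | 75.4% |
| C | .0473 | 78.9% | .0420 | 83.5% |

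**Step 5: for scale only.** Keeping 210 complete cases at 70% retention would need 210/0.70 = 300 enrolled.

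**The case against.** **The test behind .046 is not stated.** The planned treatment contrasts make a 1-df test at alpha .05 an ordinary reading. It needs only 173 complete cases, or 173/210 = 82% retention. On that reading the sentence tolerates about 18% loss and roughly holds at 3 months. If imputation recovered half of what is missing, it would just hold at 12 months too. This stands as a reason to make the claim conditional. It does not remove the gap: the article credits .046 to 210 and not to 173, and 147 complete cases still give .054 and 73% power.

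**The 70% is a floor, and 12 months is not where the superiority hypothesis sits.** This also stands. The .067 is the unfavourable end at the latest visit. The 3-month shortfall is likely to be smaller, but it cannot be fixed because retention there is not given.

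**A reader might infer that calling .046 small is itself an error.** The documents set no threshold. On the usual benchmarks (.02 small, .15 medium; taken from outside the documents), .046 lies between the two and nearer small, and the exact value is printed beside the word. The label is loose, not wrong.

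**A reader might also infer that the trial cannot see differences under half a standard deviation.** That conversion needs assumptions which the article does not give. For two arms with the third midway, d = √(6 × .046) = 0.53, but in residual SD after baseline adjustment. With two arms equal and one different, d = √(4.5 × .046) = 0.455. In raw SD both are smaller if baseline predicts outcome.

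**An article may leave alpha and df to the full protocol.** That excuses their absence. It does not excuse a printed sensitivity figure that the retention target in the same paragraph undercuts.

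**Conclusion.** The point holds in a limited form. Assuming 80% power, the two readings that reproduce .046 at 210 both require complete information on everyone enrolled, and no attrition allowance is stated. At the planned 12-month floor of 147 complete cases, the detectable f² is about .066 to .067 and power for .046 is about 63%. Under a 1-df test at alpha .05 they are .054 and 73%. A 12-month complete-case shortfall therefore appears on all three readings, and its size depends on which was meant.

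These are bounds. Imputation moves the effective sample some way from 147 towards 210, by an amount the documents do not let one fix. At 3 months, with retention assumed at 80–90%, the first two readings give about .058 to .051 and 69–75% power; the third gives .047 to .042 and 79–84%.

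The documents do not support going further, to say that the sample size is wrong or that the 3-month comparison is seriously underpowered. The defect is a stated property that the design does not have at 12-month follow-up on the most likely readings.

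**What to change.** Reword Sample Size and Retention without changing N:
- State the alpha, power and tested df behind .046.
- Say that .046 assumes complete information on all 210.
- Add the detectable f² at the planned 12-month retention: about .067 at 147 complete cases under the 2-df reading, or the matching figure if another test was meant. Note that imputation may improve on this only as far as baseline and earlier visits predict the missing outcomes.
- Add a range for 3 months, labelled as resting on assumed retention (about .058 to .051 at 80–90% under the first two readings).

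The word small can stay, and no conversion to SD units is needed. The change is wording only and affects neither conduct nor analysis. Its one cost is a slightly less favourable stated figure.

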### Ethics

Ethics approval to conduct this project was granted by the Uniting Care Health Human Research Ethics Committee (#[name]9111) and the Queensland University of Technology Human Research Ethics Committee (#1100000783).

## Results

This trial is currently underway with funding support from the Wesley Research Institute in Brisbane, Australia.

## Discussion

Results from this trial will provide information on the efficacy, practicality, and user perspectives on the effects of such a program and the success of its dissemination within the Australian context. A 12-month follow-up period will provide data on the maintenance of effects from the programs as well as patterns of usage over time and the relationship of these variables to study outcomes.

Previous trials of diabetes self-management Web-based programs have indicated that a common limitation of such programs is reduced user engagement over time [36,54,64]. It is expected that ongoing access to interactive tools and self-monitoring that users can apply to issues with self-management and dysphoria as they arise will help to maximize engagement and retention. Fortnightly email reminders may also assist users to keep on track of their program usage and prompt continued user engagement with the program [65]. Follow-up assessments during the trial will ask about usage of other treatments and website resources, but the validity of those reports cannot be guaranteed.

Results will provide information about the effectiveness of using a self-guided approach to a Web-based type 2 diabetes self-management intervention. Limitations to generalizability that commonly affect studies conducted within specific clinical or experimental settings are avoided [64] by providing nationwide access and enabling the intervention to be conducted at any location from which access to the Web via a computer is possible. As well as assessing whether the OnTrack Diabetes program will improve type 2 diabetes self-management and dysphoria, this trial is intended to serve as a source of information about the successes and shortcomings entailed in implementing such a program. Results will provide information on which future trials of Web-based cognitive behavioral therapy interventions can build in terms of processes that enhance and those that impede the practicality and rigor of research in this domain.

## Appendix

Multimedia Appendix 1 Measures used in trial.

## Abbreviations

FIT: Functional Imagery Training
RCT: randomized controlled trial
SCT: social cognitive theory
